# Background and rationale

## 1.1 Introduction

Insulin resistance is central to obesity, type 2 diabetes, dyslipidaemia and cardiovascular disease. Epidemiological studies indicate that visceral adiposity is a better predictor for insulin sensitivity as assessed by the euglycaemic hyperinsulinaemic clamp than body mass index (BMI) in different ethnic groups (1, 2) suggesting that location of fat deposition - not only the amount of fat - is critical for insulin resistance. Besides intraabdominal fat deposition and increase in lipid content in non adipose tissue (“ectopic”) such as in myocytes (intramyocellular lipids; IMCL) and hepatocytes (intrahepatocellular lipids; IHCL) has been implicated in impaired insulin action (3-7).

IMCL are important fuel stores in skeletal muscle (8, 9). The association between IMCL and insulin resistance has not been fully elucidated. Theoretically, IMCL depend on (i) the amount of free fatty acids (FFA) which is taken up into the skeletal muscle (ii) the capacity of the skeletal muscle to synthesise or, (iii) to degrade IMCL and (iiii) the ability to oxidise FFA. Recent evidence suggest that mainly a reduced capacity to oxidise IMCL contributes to impaired insulin signalling and, therefore, to peripheral insulin resistance (10). The decreased oxidative capacity, in turn, may be related to a decreased number of mitochondria, which may explain the increase in insulin resistance with age (4), or to a dysregulation of IMCL metabolism, which may be caused by an inherited defect in mitochondrial oxidative phosphorylation as shown in healthy young offsprings of parents with type 2 diabetes (3),(11, 12).

An increased hepatic fat content is a common feature in insulin resistance which can ultimately lead to non-alcoholic steatohepatitis (NASH) and cirrhosis (13). However, the underlying pathophysiology is not completely understood. Possible mechanisms include (i) an increase in FFA flux from endogenous stores, especially adipose tissue (subcutaneous and visceral) and their deposition in the liver (14), (ii) an increase in nutritional fat intake (15), (iii) de novo hepatic lipogenesis and (iiii) a reduced hepatic fatty acid oxidation (16). Importantly, recent evidence suggests that the hepatic fat content (IHCL) may be an important determinant of hepatic insulin resistance (i.e. suppression of gluconeogenesis) (17, 18) and can be influenced by weight loss (19) and insulin sensitising agents (6).

Quantitative assessment of IMCL and IHCL using chemical analysis of biopsies was fraught with a large variability (20, 21). Indirect measurements of fat metabolism using indirect calorimetry and tracer methodology was often based on assumptions (22). The non-invasive assessment of IMCL and IHCL using ^1^H-Magnetic resonance spectroscopy (^1^H-MRS) allows to reliably determine IHCL and IMCL quantitatively (20, 21, 23-26). In addition, whole fat distribution including visceral fat tissue distribution can been assessed using MRI-scan (18))

Diet and physical activity impact on insulin action. Insulin, in turn, can be considered as a key hormone regulating lipid metabolism: It promotes hydrolysis of dietary chylomicrones by stimulating lipoprotein lipase activity (27) and inhibiting hormone sensitive lipase in adipose tissue thereby decreasing FFA availability in the circulation (27). Insulin-antagonistic hormones such as GH modulate these actions directly and indirectly and may, therefore, also regulate fat tissue distribution, IMCL and IHCL (28).

Adult patients with GH-deficiency present with features of insulin resistance (29) and hypopituitarism is associated with increased cardiovascular risk (30). Adult GH-deficiency, usually a consequence of a pituitary tumor and its treatment, is a unique clinical condition that allows to study metabolic effects of GH in adult patients.

By administrating GH to GH-deficient patients the impact of GH on fat tissue distribution fat mass, IHCL and IMCL as well as peripheral and hepatic insulin resistance can be assessed. The current knowledge of diet and exercise on fat deposition as well as the impact of GH and insulin on fat mass, IMCL and IHCL is summarized below.

## 1.2 Diet and fat deposition

There is a rapidly growing epidemic of overweight people in the Western world in parallel with insulin resistance and type 2 diabetes (31). Besides physical inactivity high calorie intake contributes to this epidemic (32). On the other hand it is well established that hypocaloric diet results in a reduction of subcutaneous and visceral fast mass (33, 34) in parallel with an improvement of insulin sensitivity (33).

IMCL can be considered as plastic and dynamic fuel reserve within the skeletal muscle that responds to different physiological demands. For example, IMCL stores in physically active subjects are enlarged, rapidly repleted following high fat diet and positively correlated with peripheral insulin sensitivity (35-39). In contrast, sedentary patients with features of insulin resistance (i.e. obesity, type 2 diabetes) exhibit an IMCL content which is increased (like in athletes), but negatively correlated with peripheral insulin sensitivity (40-45). These findings further substantiate the hypothesis that not the amount of IMCL impact on insulin sensitivity but rather the capacity to utilize (i.e. oxidise) IMCL is critical in mediating insulin resistance (16) (46), (47). Importantly, a similar intake of total energy/day, but with a low fat content (15% of energy intake) does not result in an increase in IMCL whereas a high fat diet (i.e. 55% of energy intake) leads to a replenishment of IMCL in healthy volunteers (35) indicating that quality of the diet affects IMCL. In addition, starving for 72 hours (48) resulted in an increase in IMCL in healthy lean volunteers further corroborating the hypothesis that IMCL are rapidly disposable fuel stores which adapt to different physiological situations.

In middle-aged healthy men IHCL has been shown to be tightly correlated with hepatic insulin sensitivity independent of visceral adiposity (49). In women with previous gestational diabetes, recent data indicate that the amount of IHCL is related to total and saturated fat intake suggesting that not only endogenous fat availability but also exogenous fat intake may impact on IHCL (15). These findings are further substantiated by the observation that a hypocaloric diet results in a reduction in subcutaneous and visceral fat mass but also in a substantial decrease in IHCL (19).

## 1.3 Exercise and fat deposition

Physical activity has an important role in the therapy of overweight patients and is a key factor for the prevention of type 2 diabetes (50, 51). If exercise (aerobic or anaerobic) leads to a reduction in weight, the associated fat loss is usually generalised and not confined to visceral adipose tissue (52). Nevertheless, the improved metabolic parameters (i.e. insulin resistance) seen in exercising obese subjects, independent of weight loss, suggest other beneficial actions (52). Possible mechanisms include an effect of exercise on IMCL (47) or IHCL without affecting total weight. Alternatively, modulating hormones, such as GH are known to be secreted during exercise (53) and may, by their metabolic action, impact on lipid stores (54).

IMCL stores are rapidly depleted during aerobic exercise in physically active subjects (35) and moderately active healthy subjects (55). In contrast, in sedentary subjects and patients with characteristic features of insulin resistance the depletion of IMCL with exercise is much less pronounced (56), probably by a decreased capacity to degrade and/or oxidise IMCL. In addition, regular exercise resulted in unchanged (56) or even increased (57) IMCL content. This further substantiates the hypothesis that IMCL are skeletal muscle fuel stores that adapt to different physiological needs.

The impact of physical activity on IHCL in relation to insulin resistance has not been investigated yet.

## 1.4 GH-deficiency, GHRT, metabolism and nutrition

GH has potent metabolic actions. On the other hand, nutrition impacts on GH secretion. GH-deficient patients are usually not diabetic but show clinical and biochemical features of insulin resistance (58, 59). In addition, protein synthesis is impaired (60) and lipolysis is reduced (61). GHRT reverses these abnormalities but further increases insulin resistance, at least after short–term treatment (29).

Conversely, GH secretion is augmented in conditions with low insulin levels (i.e. fasting, anorexia nervosa) whereas in obesity, hyperinsulinaemia is present with an increase in FFA and glucose resulting in a suppression of GH secretion. It is hypothesised that in condition of low energy intake (i.e. fasting) GH shifts energy consumption to lipid oxidation in order to preserve protein mass (62).

## 1.5 GH-deficiency, GH-replacement therapy (GHRT) and physical activity

GH-deficient patient usually present with a reduced exercise capacity and are, therefore, less physically active (63). The reduced lean body mass (29), the reduced performance of the cardiovascular system (64), the reduced oxygen transport capacity (64) and decreased intramyocellular fuel stores (65) may explain these findings.

GHRT has consistently been shown to improve exercise performance (63) mainly by increasing lean body mass (29), improving the performance of the cardiovascular system and oxygen transport capacity (64). Whether the trend for an increase in IMCL following GHRT contribute to the improvement in exercise performance remains to be established (65).

Importantly, exercise is a potent stimulus of pituitary GH secretion in healthy subjects over a broad range of age (53). In addition, GH secretion during exercise is positively correlated with exercise capacity suggesting that GH secretion can be considered as surrogate marker of physical fitness (53).

## GH-deficiency, GH-replacement therapy (GHRT) and whole body lipid depots(incl. visceral adiposity)

Numerous studies have shown that GH-deficient adults have an increased visceral fat mass and, in keeping with this finding, tend to be insulin resistant (29). Interestingly, GH-excess (i.e. patients with GH-secreting pituitary adenoma) is also associated with insulin resistance (66). It is thought that the metabolic action or/and a direct effect of GH is the leading mechanism to induce insulin resistance in acromegalic patients (67) while the increase in visceral fat mass is the main reason for the insulin resistant condition of GH-deficient patients (29). The exact mechanisms, however, are not sufficiently elucidated yet.

Using different techniques (CT scan, MRI) GH replacement therapy (GHRT) has consistently shown to decrease fat mass, in particular visceral fat mass (29, 68). However, although insulin resistance is already slightly increased in the GH-deficient patients it usually increases further with GHRT after short-term treatment (6 weeks) and returns to baseline values following 12-16 weeks therapy (69).

## 1.7 GH-deficiency, GHRT and IMCL (Fig. 1)

So far, there is no published data available on IMCL in relation to GH-deficiency or GHRT. The preliminary results of the previous SNF grant (No 3200BO-100146) with 13 patients before and after GHRT suggest that IMCL tend to be low after negative energy balance (exercise and low fat diet) and are rapidly repleted following high fat diet and physical inactivity (Fig. 2). The changes in IMCL content between the depleted and repleted condition are significantly increased in GH-deficient patients compared to normal matched controls (Fig. 3). This is in contrast to findings in overweight patients with insulin resistance without pituitary disease (42).

GHRT tended to increase IMCL content following exercise and low fat diet whereas repletion of IMCL was similar before and after GHRT. In parallel, postprandial metabolic measurements (glucose, triglycerides, insulin) suggest an increase in insulin resistance following GHRT in keeping with an earlier observation (70). Theoretically, an increased uptake of FFA and/or IMCL synthesis or a decrease in IMCL-utilisation could explain these results. Taken together these results confirm the actual concept that IMCL does not mediate insulin resistance per se and imply that besides exercise and diet GH may modulate IMCL content.

## 1.8 GH-deficiency, GHRT and IHCL

Indirect evidence using tracer methodology and the two-step hyperinsulinaemic euglycaemic clamp technique indicates that hepatic insulin resistance is impaired in GH-deficient patients (54). IHCL has been shown to be associated with serum triglycerides (TG) in obese women with previous gestational diabetes (15). GH-deficient patients often present with a dyslipidaemia characterised by an increase in TG and LDL-cholesterol (LDL-C) concentrations (29). In addition, turnover data indicate that hepatic VLDL apolipoprotein B100 (VLDL apoB) production is increased in GH-deficiency (71), consistent with findings in insulin resistant patients with type 2 diabetes (72). Since VLDL apoB secretion depends on intrahepatocellular lipid availability (73) these data indicate that IHCL may be increased in GH-deficiency. Finally, an increase in FFA flux from the enhanced visceral fat stores to the liver may contribute to the increase in hepatic lipid availability (68). Taken together, dyslipidaemia, turnover data and enhanced visceral fat stores suggest that IHCL may be increased in GH-deficiency. Reliable data on IHCL, however, are currently still lacking.

Short-term GHRT usually results in an increase in hepatic insulin resistance (54) in parallel with unchanged or slightly elevated TG levels whereas LDL-C usually decreases (29). VLDL apoB turnover data show a further increase in VLDL apoB production in parallel with an increase in VLDL apoB catabolism resulting in an unchanged VLDL apoB pool (74). Whether GHRT affects IHCL remains to be established.

Interestingly, recent observational data indicate a high prevalence of non-alcoholic fatty liver disease ultimately leading to cirrhosis and transplantation among patients with pituitary or hypothalamic disease (75). This underlines the importance of assessing IHCL and hepatic insulin resistance in patients with pituitary disease.

Figure 1

Changes in intramyocellular lipid content (repleted – depleted) in 13 GH-deficient patients before and after GH-replacement therapy and in matched control subjects

# p=0.07

# p=0.07

p<0.02

GHD delta = IMCL repleted - IMCL depleted in GH-deficient patients

# 2. Hypothesis and endpoints (Fig 1)

Visceral fat mass and “ectopic” fat deposition (IMCL, IHCL) interferes with insulin action. Physical activity and nutrition impact on lipid stores. The GH/IGF-I axis is a modulator of lipid stores, thereby regulating insulin sensitivity.

Patients with GH-deficiency have normal beta-cell function but an increase in visceral obesity. Due to the augmented availability of FFA within the portal system IHCL will be increased compared to control subjects. In contrast, due to the lack of the GH-induced lipolytic action on adipose tissue with a concomitant decrease in FFA availability within the peripheral circulation, IMCL will be reduced. Accordingly, hepatic insulin resistance will be mainly impaired. GH replacement therapy will reverse these changes.

Figure 2

Working hypothesis

Growth hormone, possible impact of “ectopic” fat accumulation and insulin resistance

##

Physical activity

Diet

## Body fat stores

- Visceral fat mass
- Intramyocellular lipids (IMCL)
- Intrahepatocellular lipids (IHCL)

Hepatic and peripheral insulin resistance

GH status

Physical activity and quality of diet impact on visceral fat mass, intramyocellular lipids (IMCL) and intrahepatocellular lipids (IHCL). These fat stores are associated with hepatic and peripheral (skeletal muscle, adipose tissue) insulin resistance. Hormones impact on energy homeostasis by affecting exercise performance and/or regulating fuel metabolism, thereby adapting the subject to changing exogenous challenges. GH affects physical activity by improving cardiovascular performance. Metabolic effects of GH are anabolic relating to protein metabolism (increase in lean body mass), catabolic regarding fat metabolism (decrease in fat mass) and inducing insulin resistance in connection with carbohydrate metabolism. In contrast, hypoglycaemia, falling free fatty acids and increased amino acids stimulate pituitary GH release.

GH-deficient patients present with an increase in visceral fat mass and a tendency for reduced IMCL. GH-replacement therapy (GHRT) results in a decrease in visceral fat mass and a trend for an increase in IMCL. The effect of GH-deficiency and GHRT on IHCL is unknown.

## 2.1 Primary endpoints of the study are:

1. To define visceral fat mass and “ectopic” fat deposition in patients with GH-deficiency in response to exercise and diet compared to control subjects and physically active subjects.
2. To investigate the association between “ectopic” fat deposition and measurements of peripheral and hepatic insulin resistance in patients with GH-deficiency compared to control subjects and physically active subjects.
3. To determine the effect of GHRT in GH-deficient patients on “ectopic” fat stores in response to exercise and diet.
4. To examine the association between changes in “ectopic” fat stores following GHRT and changes in systemic measurement of peripheral and hepatic insulin resistance.

## 2.2 Secondary endpoints:

1. to assess the physical activity in GH-deficient patients compared to sedentary control subjects and physically active subjects

2) to measure the effect of GHRT on exercise capacity in GH-deficient patients

#

# 3. Study design

This is a prospective single-centre open case-control study. The study will be performed according to the declaration of Helsinki, the guidelines of good clinical practice (GCP), the Swiss health law (HMG dated 15 December 2000 and 27 November 2001) as well as the ordinance on clinical research (dated 17 October 2001). The study will be performed at the University Hospital of Bern. Investigations are located in the rooms of the Division of Endocrinology, Diabetes and Clinical Nutrition (located in the Children’s Hospital, U1) and in the MRI-Centre

# 4. Study population

## 4.1 Patients

Patients with hypopituitarism of the outpatient clinic of the division of Endocrinology and Diabetes of the University of Berne, Inselspital, will be tested for GH-deficiency according to the recommendations of the growth hormone research society (76). A total of 18 patients with adult GH-deficiency will be recruited.

## 4.2 Inclusion criteria

- Male and female patients with proven GH-deficiency defined as a peak GH of less than 3mU/l during an insulin provocation test with nadir plasma glucose less than 2.2 mmol/l and additionally, stable conventional replacement therapy including corticoids, thyroxin and gonadale hormones as needed.
- Ability to perform an exercise test on a treadmill or a walking band.
- Willingness to participate in the study and to give written informed consent.

##

## 4.3 Exclusion criteria

- Active neoplasia
- Severe cardiovascular disease (unstable coronary heart disease, heart failure NYHA III-IV)
- Type 2 Diabetes mellitus
- Haemophilia or other coagulation disorder
- Inability to exercise
- Contraindications to exposure to a 3-T magnetic field (Pace-Makers, osteosynthetic material)
- Pregnant women
- Women in childbearing age unless on a continuous contraceptive therapy or surgically sterilised.
- Abnormal liver or renal function (Creatinine >130μmol/L, normal reference 45-93μmol/L; ASAT and ALAT > 3 times the upper reference limit).
- Major depression, psychosis and other severe personality disorders
- Excessive alcohol consumption (>60g/d) or drug-abuse
- Refusal to give written consent
- Patients, who are not suitable for the study according to the study physician

## 4.4 Control population

Twenty age, gender and BMI matched sedentary (without regular sports activity) subjects will be recruited.

Twenty physically active healthy volunteers will be studied. Criteria for inclusion are: minimum 30’ of exercise 3 times per week and VO_2 max_ > 50 ml O_2_/kg/min for males and >40 O_2_/kg/min for females.

# 5. Intervention

Therapeutical intervention include GHRT in GH-deficient adults. This indication is accepted by Swissmedic. In addition a dietary intervention (additional fat snacks) and a controlled physical activity (determination of VO_2max_ and cycling at 50% VO_2max_ ) will be performed.

# 6. Schedule, investigation methods and data acquisition

## 6. 1 General overview (Figure 3)

Figure 3 Clinical Protocol

= equilibrated weight maintaining diet

= minimum 7 days between V1 and V2. no physical activity, equilibrated weight maintaining diet

= minimum 7 days between V2 and V3. High fat diet three days before V3**;** No exercise, food diary.

= usual clinical care: 6 months hypopituitary patients: monthly visits (IGF-I and Bioimpedance measurements)

V1 = Visit 1: determination of VO_2max_ (Spiroergometry). Nutritional advice. Food diary, Familiarization with study protocol (i.e. treadmill)

V2 = Visit 2 Two-step hyperinsulinaemic euglycaemic clamp with stable isotopes (d-[U-^13^C]glucose and d-[6-6-^2^H_2_]glucose)

V3 = Visit 3 MRS/MRI (IMCL, IHCL, visceral fat mass), repleted.

1.5 hour physical activity (bicycle) at VO_2max_ 50-55%, GH secretion profile

MRS/MRI (IMCL, IHCL), depleted

V4 identical to V1 without familiarization

V5 identical to V2

V6 identical to V3

V1

V2

V3

V4

V5

V6

Identical investigations will be performed before and after an intervention. GH-deficient patients will be studied at baseline and after 6 months GH replacement therapy. Sedentary matched control subjects and physically active subjects (road or cross-country cyclists, duathletes, and triathletes; VO_2max_ > 50mL/O_2_/kg) will be tested once.

Investigations include a) determination of exercise capacity (VO_2max_), b) measurements of “ectopic” fat deposition (IMCL, IHLC) and visceral fat mass using MRS and MRI, respectively, in repleted (no physical activity, high fat diet) and depleted (after physical activity) condition. GH secretion profile will be obtained during a standardised exercise. c) hyperinsulinaemic euglycaemic clamp in combination with stable isotope technique and indirect calorimetry to measure hepatic and skeletal muscle insulin resistance and fuel oxidation (77).

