## Calculations of the expected effect

Data will be presented as the mean ± SD. Paired t-test will be performed in patients to assess the effect of therapeutical intervention (GHRT). Unpaired t-test will be performed between GH-deficient patients before and after GHRT and control subjects (Atheltes and sedentary controls). In particular ectopic fat depots (i.e. IHCL; IMCL, delta IMCL and visceral fat mass) will be compared before and after GHRT. Unpaired t-test will be used to analyse differences in ectopic fat depots between GH-deficient patients, sedentary control subjects and physically active subjects. Parameters, which are not normally distributed will be log transformed prior to analysis. Alternatively non-parametric tests will be used. Correlation analysis between Ectopic fat depots and measurements of insulin resistance (clamp data) will be performed using Spearman’s rank correlation coefficients. P<0.05 will be considered significant. Statistical analyses will be performed on Stata 9.1 (Stata Corporation, College Station, TX, USA), and Microsoft Excel (Microsoft Corporation, USA).

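### Sections 4.4 and 6.1 define the physically active group differently (VO2max limit for women, type of sport), in a comparator that is neither sex-matched nor adjusted for sex

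*Protocol*

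**What the plan says.** Section 4.4 (Control population) sets the entry conditions for the active group. It states "Twenty physically active healthy volunteers will be studied", and continues "Criteria for inclusion are: minimum 30’ of exercise 3 times per week" together with "VO_2 max_ > 50 ml O_2_/kg/min for males and >40 O_2_/kg/min for females".

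Section 6.1 (General overview) returns to the same group when it explains that controls are studied once: "physically active subjects (road or cross-country cyclists, duathletes, and triathletes; VO_2max_ > 50mL/O_2_/kg) will be tested once".

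Three further statements matter:

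- The patients are of both sexes: "Male and female patients with proven GH-deficiency" (Section 4.2). No sex ratio is given for any group.
- Matching is stated for the sedentary controls only: "Twenty age, gender and BMI matched sedentary (without regular sports activity) subjects will be recruited" (Section 4.4).
- The group comparison is planned as follows: "Unpaired t-test will be used to analyse differences in ectopic fat depots between GH-deficient patients, sedentary control subjects and physically active subjects" (Calculations of the expected effect). No covariate is named.

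Section 2.1 names the physically active subjects as a comparator in primary endpoints 1 and 2. Section 2.2 does so in the first secondary endpoint.

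**The concern.** Recruiters need one eligibility rule, and the protocol gives two descriptions that disagree. Two things are at stake.

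**Training level.** Section 1.2 says that IMCL stores are enlarged in physically active people and correlate positively with insulin sensitivity, and that the correlation is negative in sedentary insulin-resistant patients. A group of people exercising three half-hours a week and a group of cyclists, duathletes and triathletes may therefore differ on the measured outcome itself. This point needs no assumption about sex.

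**Sex mix.** The protocol sets a lower VO2max limit for women in 4.4, so it evidently expects lower values in women. Dropping that limit can only reduce the number of eligible women. Because patients of both sexes are compared with this group by an unadjusted t-test, a shortage of active women would make part of the patient-versus-active difference a difference between the sexes.

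**Working it through.** **1. The two descriptions side by side**

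| Feature | Section 4.4 | Section 6.1 |
|---|---|---|
| VO2max, men | >50 ml/kg/min | >50 |
| VO2max, women | >40 | >50 (no separate value) |
| Activity | at least 3 x 30 min/week, any exercise | road or cross-country cycling, duathlon, triathlon |
| Unit | per kg per min | per kg only |

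The difference in threshold affects women above 40 and up to 50. The difference in activity affects, for example, runners and swimmers of either sex.

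**2. The protocol's own figure**

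The only power calculation is the paired IHCL comparison: change 3.6, SD 4.41, 18 patients, power 90%. The effect size is 3.6/4.41 = 0.816 and the noncentrality is 0.816 x √18 = 3.46. A two-sided paired t-test at 0.05 then has power 0.904, so the 90% is reproduced. The active group does not enter this calculation.

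**3. How many eligible women would 6.1 exclude?**

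The documents give no VO2max distribution for women. Assume it is normal among the women approached, with SD 5 to 7. The share of women passing >40 who also pass >50 is P(X>50)/P(X>40):

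| Assumed mean | Share also passing >50 | Share excluded |
|---|---|---|
| 40 | 5–15% | 85–95% |
| 44 | 15–27% | 73–85% |
| 48 | 36–44% | 56–64% |
| 52 | 64–66% | 34–36% |
| 56 | 81–89% | 11–19% |

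The loss runs from about 11% to 95%, depending wholly on an unknown mean.

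**4. What would a sex imbalance do to the t-test?**

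Inputs from the documents: 18 patients ("A total of 18 patients with adult GH-deficiency will be recruited"), 20 active subjects, significance level 0.05 (taken as two-sided). Assumed inputs: the share of women in each group and the sex difference in the outcome, in within-sex SDs.

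Spurious group difference = (share of women among patients − share among active subjects) x sex difference.

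Example: (0.5 − 0) x 1 SD = 0.5 SD. A half-female patient group also has a wider spread: variance 1 + 0.5 x 0.5 x 1² = 1.25 against 1 in an all-male group. The rejection rates below come from simulating fixed numbers of men and women with no true group difference.

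| Women among 18 patients | Women among 20 active | Sex difference | Spurious difference | Rejection rate |
|---|---|---|---|---|
| 9 | 0 | 1.0 SD | 0.50 SD | 28% |
| 9 | 0 | 0.6 SD | 0.30 SD | 14% |
| 9 | 0 | 0.3 SD | 0.15 SD | 7.2% |
| 6 | 0 | 1.0 SD | 0.33 SD | 14% |
| 6 | 0 | 0.6 SD | 0.20 SD | 9% |
| 9 | 5 | 1.0 SD | 0.25 SD | 8.0% |
| 9 | 5 | 0.6 SD | 0.15 SD | 6.3% |

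A noncentral-t calculation with the same variance inflation gives 29% for the first row. At the mild end (30% women among patients, 10% among active subjects, 0.3 SD) it gives a 0.06 SD difference and 5.4%. With equal shares of women there is no spurious difference.

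**The case against.** The best defence is that 4.4 is the section that states inclusion criteria, whereas 6.1 is a parenthesis in a schedule overview with an incomplete unit. On VO2max, 6.1 describes a subset of 4.4, and an explicit limit for women shows that women were meant to be enrolled. This stands as a reason to align 6.1 to 4.4. It does not remove the conflict, because a reader of 6.1 would turn away people whom 4.4 admits.

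Second, the active group is a deliberate contrast in fitness, and the sedentary group already supplies a comparison matched on age, gender and BMI. That is fair and limits the damage. The active group is nevertheless named in two primary endpoints and tested against the patients directly.

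Third, the sport list may be intended, since the analysis section calls this group athletes. That also stands. Whether the list is a criterion is for the sponsor to say.

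A reader might go further in three ways that the documents do not support:

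- **That 6.1 removes most women.** No distribution for women is given, and the loss could be a minority if the women recruited are highly trained.
- **That 6.1 requires competitive athletes.** It names sports and says nothing about competition.
- **That the conflict is what causes confounding by sex.** The active group is unmatched under either description, so imbalance could arise with 4.4 followed exactly. The 6.1 reading can only worsen it.

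**Conclusion.** The inconsistency is real and should be corrected before recruitment. The two sections disagree on the limit for women and on the kind of activity, and 6.1 misstates the unit. Which description is followed sets the training level of a comparator in primary endpoints 1 and 2, and can affect its sex mix.

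The size cannot be determined from the documents. The illustrative false-positive range of about 5% to 28% rests on assumed shares of women and an assumed sex difference. The upper end needs half the patients to be women, no active women at all, and a full 1 SD sex difference. One might enter 0.5 SD into a unit-variance t calculation and obtain 32%, but that ignores the wider spread of a mixed-sex patient group, so 28% is the better figure for that extreme case.

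The within-patient effect of GHRT (primary endpoints 3 and 4) and the 90% power statement are untouched.

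**What to change.** 1. Make Section 6.1 repeat the Section 4.4 criteria: at least 3 x 30 min/week and VO2max >50 for men or >40 for women, in ml O2/kg/min.
2. State in 4.4 whether the list of sports is an entry criterion or only an example, and use the same wording in 6.1.
3. Recruit the 20 active volunteers to roughly the patients' male-to-female ratio, or adjust the patient-versus-active comparison for sex.

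The first two items are short text corrections. The third needs a recruitment note, with slower recruitment of active women as the small downside, or one added covariate. Recruiting to the ratio is the safer choice. If the active group had no women, the group effect in a model with group and sex would rest on the men alone. With 9 male patients the standard error would be about √(1/9 + 1/20) / √(1/18 + 1/20) = 0.401/0.325 = 1.24 times that of the full 18 versus 20 comparison at the same within-sex SD.
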